## Abstract

The role of personality trait variation in psychopathology and its influence on the outcome of psychotherapy is a burgeoning field. However, thus far most findings were based on controlled clinical trials that may only poorly represent real-world clinical settings due to highly selective samples mostly restricted to patients with major depression undergoing antidepressive medication. Focusing on personality and psychopathology in a representative naturalistic sample of psychotherapy patients is therefore worthwhile. Moreover, up to date hardly any confirmatory research has been conducted in this field. Strictly confirmatory research implies two major requirements: firstly, specific hypotheses, including expected effect sizes and statistical approaches to data analysis, must be detailed prior to inspection of the data, and secondly, corresponding protocols have to be published online and freely available. Here, we introduce a longitudinal naturalistic study aimed at examining, firstly, the prospective impact of baseline personality traits on the outcome of psychotherapy over a 6-month observation period; secondly, the stability and change in personality traits over time; thirdly, the association between longitudinal change in psychopathology and personality; fourthly, the agreement between self-reports and informant rating of personality; and fifthly, the predictive validity of personality self-reports compared to corresponding informant ratings. For it, we comprehensively state *a priori* hypotheses, predict the expected effect sizes and detail the statistical analyses that we intend to conduct to test these predictions. Such a stringent confirmatory design increases the transparency and objectivity of psychopathological research, which is necessary to reduce the rate of false-positive findings and to increase the yield of scientific research.

## Introduction

### The Importance of Personality for Public Mental Health and Psychotherapy

The global burden of disease attributable to mental disorders is tremendous (1), in particular in high-income Western societies, including Europe and the United States of America (2, 3). Targeting modifiable risk factors for severe psychopathology has therefore highest priority. Previous research has confirmed that maladaptive personality is a crucial prospective risk factor for ill-health, all-cause mortality, and social functioning deficits (4–7). Meta-analyses have further revealed that personality shows a substantial association with subjective well-being (8) and relationship satisfaction (9). Interestingly, behavioral genetics suggest that the pleiotropic genetic influences underlying personality trait variation fully account for the genetic interindividual differences in subjective well-being (10). Evidence from cross-sectional studies suggests that personality traits, in particular high neuroticism and low conscientiousness, strongly relate to psychopathology (11, 12). In longitudinal studies adjusted for baseline impairment, the prospective effect of personality traits on subsequent occurrence of psychopathology is considerably weaker but remains substantial (13–16). Moreover, evidence from several quantitative genetic studies suggests that neuroticism and internalizing disorders (i.e., depression, anxiety, and stress-related disorders) share approximately 50% of common genetic variance (17–19). Recent evidence has further demonstrated that neuroticism accounts for cognitive traits such as rumination and evaluation, which negatively impact on psychopathology (20, 21). In an attempt to quantify the economic costs attributable to both neuroticism and common mental disorders (i.e., depression, anxiety, and substance-use disorders) in the general population, Cuijpers and colleagues (22) found that the per capita excess costs for the 25% highest neuroticism scorers were approximately 2.5 time higher than the costs attributable to all common mental disorders combined. Accordingly, personality traits are considered among the most important modifiable factors influencing public health and psychiatric practice (4, 23–25). Because of its pervasive and persistent impact on (mental) health and functioning, personality necessarily needs to be considered in the planning and conduct of psychotherapy (26, 27). Indeed, original studies revealed that baseline personality significantly interferes with the course of psychopathology and the efficacy of psychotherapeutic interventions (28–30). It was further demonstrated that personality difficulties take considerably longer to treat than the common number of 15–19 sessions routinely administered in randomised controlled trials (RCT) (31, 32). In accordance, comorbid personality disorders, which can be modeled as maladaptive variants of normal personality traits (33–35), have shown to significantly reduce the treatment response in patients with mood and anxiety disorders (36–38) and to predict long-term functioning deficits and impairments (39–42). Taken together, these findings stress the importance of personality for public mental health and suggest that psychotherapy, which is the second most common treatment for mental disorders after psychotropic medication in Europe and the United States (43, 44), needs to carefully incorporate personality traits.

### What This Project Adds to the Literature

There are various gaps in the literature that need to be addressed to foster and enhance our understanding of personality effects on psychopathology over the course of psychotherapeutic interventions. So far most original studies on the influence of personality on the outcome of psychotherapy have been conducted as RCT under laboratory conditions and almost exclusively with depressed patients (28–30, 45, 46). Even though RCT are considered the gold standard to evaluate the efficacy of therapeutic interventions, they have various severe limitations, the most important being low external validity and poor generalizability (47, 48). That is, real-world effectiveness of psychotherapeutic (48) and pharmacological interventions (47) is often considerably lower than their efficacy under carefully controlled experimental conditions. There are at least two main reasons for that discrepancy. Firstly, highly selective inclusion criteria in RCT largely exclude participants with complicated comorbid disorders and personality pathology as well as patients who undergo additional treatments (48). Such a restrictive patient enrollment therefore produces biased samples with poor external validity that are not representative for the average patient seen in real-world clinical settings. Secondly, RCT are conducted strictly according to psychotherapy treatment manuals, while in real-world clinical settings therapists hardly consider and adhere to treatment manuals (49). It is therefore necessary to examine the association between personality and psychopathology in naturalistic real-world setting in order to generalize the findings from RCT. Because replication is a cornerstone of good psychological research (50–52), this is a timely objective. Moreover, almost all studies on the personality–psychopathology association conducted thus far relied exclusively on self-reports, even though self-reports and informant ratings of personality traits show only moderate agreement, in particular with respect to maladaptive neuroticism, pathological personality traits, and personality problems (53–55). Because both self- and other-reports of personality have incremental predictive validity above each other (56–58), the inclusion of an informant rating of personality functioning in the prediction of psychopathology and psychotherapy outcomes is thus worthwhile. Another important objective of the current project is to examine the stability of personality traits over the course of 6 months of psychotherapy using a longitudinal pre–post design. In community-based epidemiologic studies of personality–psychopathology associations, such a prospective design with baseline and follow-up assessment is an established standard protocol (16, 59–62), but with a few exceptions (61), these studies typically assess personality traits at baseline only. As for research in clinical samples, various longitudinal studies with pre–post assessment of personality traits have focused on the stability of personality traits in psychiatric patients (46, 63–65), but these chiefly tested the effects of antidepressive medication on personality in patients with major depression. There are, in addition, some studies focusing on the stability of personality in persons with substance-use problems (61, 66) or psychosis (67, 68), but none of these studies specifically examined outpatients undergoing psychotherapy. Because transdiagnostic psychological interventions targeted at modifying neuroticism have drawn broad interest in the research community (69, 70), focusing on the short-term stability of personality traits in unselected psychotherapy users with various diagnoses is thus worthwhile.

In sum, research has demonstrated that personality is crucial to psychopathology and public mental health (4, 71, 72). Even though some clinical psychologists have made compelling cases for the inclusion of personality in the planning and conduct of psychotherapy (26, 73, 74), the concept of personality remains largely underutilized in clinical settings (4, 27). For instance, before inception of this project, the psychotherapy institute serving as the study site that collects the data for the present project, did not apply any inventory of normal-range personality such as the five-factor model (FFM) of personality (75, 76), and this is certainly the rule rather than the exception in psychotherapy centers. Treatment protocols targeting neuroticism have been developed (69) and are now undergoing systematic evaluation (70). However, the treatment and the changeability of personality traits in psychotherapy, especially that of maladaptive personality, remain largely debated (46, 77, 78). The present research project thus aims to make several important contributions to the literature by applying a stringently objective and transparent confirmatory approach.

## Materials and Equipment

### Study Site and Sampling Procedure

All data will be collected at the Klaus-Grawe-Institute (KGI) for psychological therapy in Zurich, Switzerland, which is an outpatient psychotherapy center offering psychological therapy according to Grawe’s (79) framework of general psychology and psychotherapy. That approach aims at the comprehensive application of effective and evidence-based techniques of various psychotherapeutic orientations, including cognitive, behavioral, and interpersonal techniques. Every patient receives individually tailored treatment based on his/her individual biopsychosocial needs. As a result, each therapy is unique in its scope and application of specific psychotherapeutic techniques, which precludes the application of restrictive therapy manuals. Patients at the KGI present with heterogeneous mental health problems, including, but not limited to, depressive disorder, panic disorder, generalized anxiety disorder, post-traumatic stress disorder, adjustment disorder, acute stress disorder, burnout, substance-use disorder, eating disorder, and personality disorder. What makes this heterogeneous naturalistic sample so valuable is the fact that, in contrast to most RCT (48), inclusion is not restricted to specific psychiatric diagnoses. In fact, many clients treated at the KGI present with subclinical disorders and interpersonal problems and, accordingly, do not meet criteria for any diagnosis according to the International Classification of Disease 10th Edition (ICD-10) (80), which is in accord with the dimensional concept of mental disorders (81–83). In most clinical trials reviewed above, these patients would have been excluded, which restricts the external validity and generalizability of findings from such trials.

Collection of data will include all German-speaking patients between 18 and 65 years who started psychotherapy at the KGI in Zurich dating back to September 2015 when FFM measures of personality were included in the standard test battery. Even though therapy is also offered to English speaking patients, restriction to German-speaking patients was made because assessments in English comprise different questionnaires. Data from a comprehensive assessment at outset of the psychotherapy will be used as baseline measures. After 6 months, all patients will be reassessed with a subset of these measures unless their therapy ended prior to that. These data will be used as the 6-month follow-up assessment. Originally, we planned to reassess patients after 12 months (second follow-up), but we now came to realize that this is not feasible because there are not enough patients who remain incessantly in therapy for so long. The 12-month follow-up will therefore not be executed. Based on power analyses, we intend to proceed sampling until we have approximately *n* = 100 6-month follow-up assessments. Because sample size calculation is intricate and not readily applicable for generalised estimating equations (GEE) analysis, we relied on the following three sources: firstly, we scrutinized various sample size recommendations for correlated data published in the methodological literature (84–86); secondly, we tested different sample size estimations based on repeated measure ANOVA calculated with G*Power (87); and thirdly, we considered the significance levels for varying effect sizes as obtained from applications of GEE in our previous work (14, 88–90). The final sample size of *n* = 100 was then estimated based on all these sources for an expected moderate effect size (0.3 < *d* > 0.5), a significance level of α = 0.05 and power (1 − β) > 0.8.

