(1)BFI traits show high differential continuity over time (all *r* > 0.6). To test this prediction, we will compute bivariate Pearson correlations between trait scores at baseline and 6-month follow-up. We will provide both attenuated and disattenuated correlation coefficients corrected for scale unreliability.(2)BFI traits demonstrate substantial mean-level continuity (all *d* < 0.5). More specifically, we predict that only neuroticism will demonstrate modest mean-level change (0.2 < *d* > 0.5), while the other four traits will remain almost unaltered over time (all *d* < 0.2). These predictions will be tested with *t*-tests for paired samples by examining the differences in standardized mean-level change between baseline and 6-month follow-up.(3)Baseline BFI traits, specifically high neuroticism and low conscientiousness, substantially reduce (*d* > 0.5) the effectiveness of psychotherapy based on the BSI, GAF, and INK over the 6-month observation period. In order to test this prediction, we will compute GEE (121). These statistical models were introduced to fit regression analyses that account for within-subject correlation, which is an inherent part of longitudinal studies that rely on repeated outcome measures. Together with mixed models and random coefficient models, GEE represent the state of the art for longitudinal data analysis and are preferred to repeated measures ANOVA due to their superior psychometric properties (122, 123). The baseline BFI traits will be entered as the predictor variables and the repeated measures of the BSI, GAF, and INK successively as the outcome. The effect size of interest will be modeled as the interaction term between baseline personality and the time slope coefficient of the repeated outcomes, that is, the linear time trend for change in BSI, GAF, and INK. By simultaneously adjusting for the intercept, such a statistical modeling ensures that change in psychopathology over time is estimated independent of baseline impairment. These models will be conducted with and without adjustment for baseline diagnoses based on ICD-10.(4)Mean-level change in BFI traits is only weakly, if at all, correlated with change in psychopathological impairment over time (all *r* < 0.3). To test this hypothesis, we will compute individual change scores over time for all repeated measures by subtracting the baseline score from the follow-up score. The change scores of the BFI traits will then be correlated with the change scores of the BSI, GAF, and INK using Pearson correlation.

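### The power above 0.8 claimed at n = 100 for d of 0.3 to 0.5 does not hold across that range for the personality-by-time tests, under the usual meaning of d

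*Protocol article*

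**What the plan says.** Under Study Site and Sampling Procedure, the Protocol article plans that "we intend to proceed sampling until we have approximately *n* = 100 6-month follow-up assessments". The reasoning opens with the analysis to be served: "Because sample size calculation is intricate and not readily applicable for generalised estimating equations (GEE) analysis". It then names three sources: published recommendations for correlated data, the authors' earlier GEE work, and G*Power ("we tested different sample size estimations based on repeated measure ANOVA calculated with G*Power (87"). The result is stated for an "expected moderate effect size (0.3 < *d* > 0.5), a significance level of α = 0.05 and power (1 − β) > 0.8". The 12-month assessment has been dropped, so each outcome has two time points.

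Under Hypotheses and Planned Analyses, GEE appears in hypothesis 3 of the first paper and hypotheses 2 and 3 of the second. In each, the tested term is a moderation effect: "The effect size of interest will be modeled as the interaction term between baseline personality and the time slope coefficient of the repeated outcomes". Hypothesis 3 of the first paper and hypothesis 2 of the second predict d > 0.5 for that term.

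The article does not say which ANOVA effect was powered, how d is defined for a continuous moderator, whether the test is one- or two-sided, or what pre-post correlation was assumed.

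**The concern.** A repeated-measures calculation can power two different things with the same n: the average change within patients, or the difference in change between patients who score high and low on a trait. The second is much harder to detect at the same nominal d. The article attaches its power figure to the GEE analysis, which tests the second, but the figure looks like one for the first.

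The article presents itself as strictly confirmatory and says its results may corroborate or disconfirm the role of personality. If a moderation test comes out null, readers will weigh that null against the stated power. For effects in the stated range, the real power could be well below 0.8. The printed range is also malformed: "expected moderate effect size (0.3 < *d* > 0.5" literally says only that d exceeds 0.5. Hypothesis 2 of the first paper repeats the pattern with 0.2 and 0.5.

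**Working it through.** **Inputs from the article:** n = 100 completed follow-ups, alpha 0.05, power above 0.8, d printed as 0.3 < d > 0.5 (read here as 0.3 < d < 0.5), two time points.

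**Assumptions, because the article does not give them:** a two-sided test (one-sided also shown); d in SD of the change score (raw outcome SD also shown, with pre-post correlation ρ from 0 to 0.8); complete pairs; no multiplicity adjustment.

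**1. Reproducing the stated figure.** For within-person mean change, the paired t-test has noncentrality d√n on 99 df. At d = 0.3 this is 0.3 × 10 = 3.0, and power is 0.84. At d = 0.4 and 0.5 power is 0.98 and above 0.99. The smallest d with 80% power is 0.28, and 90 patients would suffice at d = 0.3. The claim of power above 0.8 is therefore reproduced for mean change.

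**2. The moderation test.** With two time points and complete pairs, the personality-by-time coefficient is the regression of the change score on the baseline trait. Expressed as a contrast between two halves of 50, the noncentrality is d√(50/2) = 5d on 98 df, half that of the paired test. The equivalent correlation is r = d/√(d² + 4).

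| d | r | 5d | Power, two-sided | Power, one-sided | n for 80%, two-sided |
|---|---|---|---|---|---|
| 0.3 | 0.148 | 1.5 | 0.32 | 0.44 | 351 |
| 0.4 | 0.196 | 2.0 | 0.51 | 0.63 | 199 |
| 0.5 | 0.243 | 2.5 | 0.70 | 0.80 | 128 |

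Fisher's z gives 0.31, 0.50 and 0.68 (two-sided), and a simulated robust-SE test gives 0.34, 0.54 and 0.73. Two-sided power reaches 0.80 at d of about 0.57 (r of 0.27 by noncentral t, 0.28 by Fisher's z).

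**3. If d is in raw outcome SD.** The SD of change is then √(2(1 − ρ)), and d is divided by it before step 2 is applied (two-sided):

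| ρ | d = 0.3 | d = 0.4 | d = 0.5 |
|---|---|---|---|
| 0 | 0.18 | 0.29 | 0.42 |
| 0.5 | 0.32 | 0.51 | 0.70 |
| 0.7 | 0.48 | 0.73 | 0.89 |
| 0.8 | 0.65 | 0.88 | 0.97 |

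At d = 0.3, power reaches 0.80 only if ρ is about 0.86 or more.

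**4. Readings under which the claim holds for moderation.**
- *d as 2f of a G*Power within-between interaction.* With f = 0.15 and ρ = 0.5, the noncentrality is f² × N × 2/(1 − ρ) = 0.0225 × 100 × 2/0.5 = 9, whose root is 3.0, giving power 0.84. In a two-by-two design, however, f = 0.15 is a difference in change of 4 × 0.15 = 0.6 SD between the halves, twice the named d.
- *d as a standardised slope.* A coefficient of 0.3 at n = 100 gives power 0.88 by regression and 0.86 by Fisher's z.

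**The case against.** The strongest reply is that the article does not predict 0.3 to 0.5 for these tests. It predicts d > 0.5, and two-sided power there is 0.70 at 0.5, 0.78 at 0.55, 0.81 at 0.57 and 0.84 at 0.6. This stands, and it narrows the point considerably: for the predicted effects the shortfall covers only about 0.50 to 0.57. It also shows that the powered range and the predicted effect do not match.

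Second, the inputs are not fixed. The hypotheses are directional, and a one-sided test brings d = 0.5 to 0.80. A high pre-post correlation rescues the upper part of the range if d is in raw SD. Patients with only a baseline may add some information, though little: with 150 baselines, power at d = 0.5 rises from 0.70 to about 0.74. Hence the exact figures are conditional. None of these changes rescues d = 0.3 unless ρ is about 0.86 or more.

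Third, a reader might infer that the stated power can only have come from a within-person calculation. The documents do not support that. A within-between interaction with d taken as 2f, which belongs to the class of calculation the article names, also gives 0.84, and hypothesis 3 of the second paper does compare standardised coefficients. Since the article prints d without defining it, these readings are possible but not established.

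Fourth, the article condenses a fuller protocol, and two of its three sources for n are external. Missing ANOVA inputs alone would be no finding. The point concerns a figure that the article does state.

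**Conclusion.** The stated power is not delivered across the stated range for the tests it is presented as serving. Under a two-sided 0.05 test with d in SD of change, power for moderation is about 0.32 at d = 0.3 and 0.70 at d = 0.5, not above 0.8. The shortfall is large at the lower end and small at the top. The claim is sound for mean change within patients.

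A reader might go further and conclude that a null on the main hypothesis has a 30 to 69% chance of being a miss. That does not follow: the article names no main hypothesis, the percentages apply to effects smaller than those predicted for moderation, and they depend on assumptions that the article leaves open. Nor does the point show that n = 100 is wrong for the study. It shows that one power statement is being used for two kinds of test and is correct, under the usual meaning of d, for only one of them.

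**What to change.** Leave n unchanged and revise the text:

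- Correct the range to 0.3 < d < 0.5, if that is what was meant, and correct the same pattern in hypothesis 2 of the first paper.
- Define d for a continuous moderator, and state sidedness and the assumed pre-post correlation.
- Report power separately. Under a two-sided 0.05 test with d in SD of change, 100 completers give at least 0.80 power for within-person mean change of d about 0.28 or more. For personality-by-time effects they give 0.80 only from d about 0.57 (r about 0.28), with about 0.32 to 0.70 for d of 0.3 to 0.5. If another definition of d was used, give the matching figures.
- Reconcile the range used for sample size with the d > 0.5 predicted in hypothesis 3 of the first paper and hypothesis 2 of the second.

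The cost is a less favourable power statement for the moderation tests. No extra patients and no change of analysis are needed.
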